
#### Physical Fitness Tests

For the purpose of this study, selected tests from the Eurofit fitness battery [46] will be utilized:

Cardiorespiratory fitness of children will be measured with the 20 m shuttle run test by Léger et al [47]. In brief, a 20 m flat course, measured by tape and marked with cones will serve for the test. A total of 10 tracks are set. The prerecorded sound signals are played to the children, and they are prompted for the test run in 2 intervals (2x 20 m). Once the children are familiar with the test procedures, they are invited to run back and forth in groups of 10, following the preset pace of the sound signals. Starting at a speed of 8.5 km/h, the frequency of the signal is gradually increased so that the speed increases by 0.5 km/h from 1 min to the next. If children cannot follow the signal and do not reach the 20 m line for 2 consecutive intervals, they will be asked to stop the test and the distance traveled (in full laps) will be recorded. To calculate cardiorespiratory fitness, the number of laps is converted to a speed value, and along with the participant’s age, used in the formula provided by Léger et al [47] to estimate the maximal oxygen uptake (VO_2_ max; ml x kg^-1^ x min^-1^).Upper body strength will be determined using the handgrip resistance test, which measures the maximum isometric grip force. The field investigator will demonstrate how to grip the dynamometer. Each participant will have 1 preliminary trial per hand (with a 30-sec rest in between) to grip the dynamometer as hard as possible. In addition, the dominant hand will be noted. The participants will remain in a standard bipedal pose with their shoulder adducted and neutrally rotated, elbow flexed at 90 degrees, forearm in neutral position holding the Saehan hydraulic dynamometer (MSD Europe BVBA; Tisselt, Belgium) without making contact with any body part. The dynamometer will be adapted to the hand size of each participant, and the maximum readings of 6 trials (measured to the nearest 0.1 kg, 3 trials per hand) will be recorded. The highest score will be used as the final result. Higher values indicate better performance.

#### Objective Activity Measurements

Physical activity behavior will be assessed with an ActiGraph wGT3X-BT accelerometer [48]. Participants will be instructed to wear the device at all times (except during activities involving water contact) for 7 days around the hip. The measured period will include 5 school days and 2 weekend days. Devices will run on the most recent firmware version (version 1.9.2 at the time of writing) and will be initialized with the ActiLife version 6.13.3 (Actigraph LLC) at a sampling rate of 30 Hz. Analyses will be performed using the ActiLife software.

#### Cognitive Performance

In cooperation with the schools, the school exam grades for the following subjects will be obtained: English, mathematics, home language, and life skills. The sum score of these 4 subjects will be used to estimate the academic achievements. In addition, we will obtain school schedules to monitor the overall academic progress of the children. A school schedule is a quarterly summative tool used by schools to measure and track the progress of the learners, across all their subjects, in an academic year. In addition to tracking the child’s progress in the grade, the school schedule is used at the end of the academic year to determine whether the child will proceed to the next grade or be retained in the present grade.

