### Study Area

The study will be conducted in historically black and colored primary schools in Port Elizabeth townships (Motherwell, Zwide, Kwazakhele, and New Brighton) and northern areas (Schauderville, Bethelsdorp, Windvogel, and Booysens Park), which form part of the Nelson Mandela Bay Municipality (Figure 2). These schools and communities are characterized by poverty and high unemployment rates. They represent the typical institutional and teacher-related PE barriers faced by the schools [34], including (1) shortage of qualified, accountable, and engaged PE teachers; (2) PE is marginalized as priority–it lost its standalone subject status in 1997 and is placed within the life skills and life orientation learning area, as more importance is given to other (examinable) subjects; (3) teachers lack the ability to integrate PE with other study areas within the life skills and life orientation subject (personal and social well-being, creative arts, and PE); (4) large class sizes; (5) insufficient and inadequate infrastructure and equipment; and (6) safety and security challenges.

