#### Component 1: KaziKidz and KaziHealth Teaching Material

It is a holistic education and instructional tool designed for primary school teachers. This teaching material was pilot tested at 2 elementary schools in the Port Elizabeth area in August 2018. Feedback from teachers was obtained and the material revised accordingly. Through the implementation of 3 content pillars—(1) PE, (2) moving-to-music, and (3) health and hygiene and nutrition education lessons—the toolkit aims to enhance children’s overall health in disadvantaged South African primary schools. The *KaziKidz* teaching material consists of lesson plans within each of the 3 content pillars. The lessons have been designed in line with South Africa’s Curriculum and Assessment Policy Statement. Ready-to-use assessments can be found at the end of each section, which may be integrated into formal assessments of children’s performance and can complement the school's academic curriculum. The purpose is to lead children through content, games, and activities, partly supported by music and conducted in a joyful manner that encourages and promotes a healthy lifestyle throughout childhood and into adolescence. *Kazi* (an animated active mascot, designed to encourage children to participate in *KaziKidz*) and lesson plans will guide teachers through the teaching material. We expect that by using the *KaziKidz* teaching material, teachers will contribute to further the health and well-being of the children they teach and educate.

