### Study Participants

The effect of the *KaziKidz* teaching material will be evaluated in 1 randomly selected class in grades 4, 5, and 6 (=intermediate phase) in each of the 8 study schools (interventions are randomly assigned to any of the 4 northern area or 4 township schools) even though *KaziKidz* teaching material will be offered to all classes in grades 1 to 7 as part of the life skills and life orientation courses in the school curriculum.

For *KaziHealth*, all teachers from the 8 schools will be invited to participate in the program. All participating teachers will undergo the full health risk assessment, and teachers at the intervention schools will have the option to participate in the 20-week intervention. The teachers from the control schools will be offered the intervention program after the completion of the study.

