### Assessment Methods

Primary outcomes for the *KaziKidz* testing battery include (1) anthropometric and clinical examinations, (2) physical fitness and self-reported and objectively assessed activity, (3) cognitive and academic performance, and (4) questionnaire for assessment of psychosocial health. Primary outcomes for the *KaziHealth* testing battery include (1) anthropometric and body composition assessments, (2) clinical examinations, (3) self-reported and objectively assessed physical activity and physical fitness, and (4) questionnaire results from psychosocial health assessment. Further measures include diet and nutritional analysis with the 24-hour dietary recall. Secondary outcomes for both tests are gender, ethnicity, SES, age, weight, and height. Figure 7 summarizes the assessment methods to be utilized in this study. For baseline and follow-up surveys, the same scientifically recognized procedures will be selected and conducted by professional staff, adhering to standardized, quality-controlled protocols.

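### The academic-achievement score includes the life-skills mark, although KaziKidz is taught within life skills and supplies assessments that schools may count towards marks, so one of the four marks can differ in meaning between arms

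*Protocol article*

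**What the plan says.** **The outcome.** The Assessment Methods section lists, among the KaziKidz primary outcomes, "3) cognitive and academic performance". The Cognitive Performance section says where the marks come from: "In cooperation with the schools, the school exam grades for the following subjects will be obtained". It then names the subjects and the score: "English, mathematics, home language, and life skills. The sum score of these 4 subjects will be used to estimate the academic achievements". The only other source given for this domain is the quarterly school schedule, which covers all subjects. No test administered by the study is described.

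**The intervention.** The Study Participants section describes how the KaziKidz toolkit reaches the children: "offered to all classes in grades 1 to 7 as part of the life skills and life orientation courses in the school curriculum". The Study Area section says that physical education "is placed within the life skills and life orientation learning area". On the toolkit's contents, the Component 1 section says: "Ready-to-use assessments can be found at the end of each section, which may be integrated into formal assessments of children’s performance". The Component 2 section adds that the workshops explain both the lessons and the assessments to teachers, so in two intervention schools teachers are shown how to use them.

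**The control arm.** The Study Design section describes only the documentation of routine physical education and sports. The Results section gives control schools the intervention materials once the study is over.

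**The concern.** A score meant to show general academic achievement should be measured in the same way in both arms and should not be built partly from the subject that the intervention teaches. Here one of its four parts is the mark in that subject. This opens two routes to a difference in the sum without any change in English, mathematics or home language:

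1. **Instrument.** If intervention schools use the toolkit's assessments for formal marks, the life-skills grade rests partly on different tests in the two arms.
2. **Content.** Even with identical tests, intervention children are taught the KaziKidz content in that course. A higher life-skills mark may be real learning, but it is learning of what was delivered.

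Either way, an apparent academic effect could be reported within a primary outcome domain when achievement in the other subjects has not moved.

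**Working it through.** **Step 1: does the chain hold in the text?**

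| Link | Where stated | Strength |
|---|---|---|
| Academic performance is in a primary domain | Assessment Methods | explicit |
| Life skills is one of four summed marks | Cognitive Performance | explicit |
| KaziKidz is taught within life skills | Study Participants; Study Area for physical education | explicit |
| Toolkit assessments can enter formal marks | Component 1 | permitted, not required |
| Only intervention schools have the toolkit during the trial | Study Design, Results | explicit |
| A rule keeps toolkit assessments out of the outcome marks | nowhere in the article | absent |

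The content overlap is close. The Study Area section divides life skills into personal and social well-being, creative arts, and physical education. The three KaziKidz pillars are physical education, moving-to-music, and health, hygiene and nutrition.

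**Step 2: would the planned model remove the difference?** Analysing change from baseline, or adjusting for the baseline value, deals with differences that existed before randomization. This one arises afterwards. Random intercepts for class and school deal with clustering, not with a shift that runs along the arm indicator.

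**Step 3: the plan's own scale.** The point disputes no stated figure, but the power statement gives a yardstick. Inputs from the Sample Size and Randomization section: effect 0.5σ, intraclass correlation 0.04, 100 children in each of 4 schools per arm, 5% level (taken as two-sided).

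- Design effect = 1 + 99 × 0.04 = 4.96; effective n per arm = 400 / 4.96 = 80.6.
- SE of the difference = √(2 / 80.6) = 0.157σ; 0.5 / 0.157 = 3.175.
- Power = Φ(3.175 − 1.96) = 88.8%, which agrees with the stated figure of over 85%.

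(With a t reference on 6 degrees of freedom the power is about 75%. That is a separate matter.)

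**Step 4: illustration of size.** Assumptions not in the document: the four marks have equal SD s, every pair has correlation r, and there is no true effect on any subject. A shift of b SDs in life skills alone moves the sum by b·s. The variance of the sum is 4s² + 12rs², so

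shift in the sum, in SDs of the sum = b / √(4 + 12r).

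- r = 0.5: √10 = 3.16
- r = 0.7: √12.4 = 3.52

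| b (life skills only) | r = 0.5 | r = 0.7 |
|---|---|---|
| 0.25 | 0.079 | 0.071 |
| 0.5 | 0.158 | 0.142 |
| 1.0 | 0.316 | 0.284 |

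To set these against the planning effect, s and r must be read as the SD and correlation of the changes, and the intraclass correlation of 0.04 must apply to this score. On that reading, with SE 0.157, a shift of b = 0.5 would give a significant result about 17% (r = 0.5) or 15% (r = 0.7) of the time by the normal approximation, and 14% or 12% with t on 6 degrees of freedom, against a nominal 5%. With b = 0.25 the normal figures are about 8% and 7%. Reaching the full 0.5σ through life skills alone would need b = 0.5 × 3.16 = 1.58 to 0.5 × 3.52 = 1.76.

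**The case against.** **The wording is permissive.** A reader might infer that the outcome is in fact measured differently in the two arms, with a quarter of it switched to the intervention's own tests, set and marked by the teachers who deliver it. The article does not support that. The toolkit's assessments may be used, but no uptake is given. The outcome is drawn from exam grades, and nothing says that end-of-section assessments enter them. The article does not say who marks the assessments. Life skills also has several study areas, so even a school that used the assessments need not base its whole mark on them. This objection stands, and it limits the first route to a possibility of unknown extent. It does not touch the second.

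**The outcome's status is mixed.** The statistical objectives tie intervention effects to disease status and other health parameters, and mention cognitive performance only in association with fitness. The listing as a primary outcome is nevertheless explicit, and the Conclusions name cognitive performance among the things the project aims to improve.

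**A better life-skills mark may be genuine.** The lessons follow the national curriculum, so the gain may be real academic learning. That is a reason to report the mark separately, not to discard it.

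**Teacher awareness affects all four marks.** This is true, and dropping one subject does not cure it. The point here is confined to what is specific to life skills.

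**An analysis plan could add a score without life skills.** It could, and the lack of such an analysis in an article is no defect. But the article itself fixes the score, and it is that definition which is at issue.

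**Conclusion.** The point holds in this form: the academic score contains the mark in the subject that KaziKidz teaches and may help to assess, in one arm only during the trial, and the article states no safeguard. Followed as written, the plan can show an academic effect without any change in general achievement. The route is confined to one of four marks.

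The document gives no basis for the size. The range of about 0.07 to 0.32 SD of the sum rests on assumed equal SDs, assumed correlations of 0.5 to 0.7, and an assumed life-skills shift of 0.25 to 1.0 SD. A reader might go on to infer that bias accounts for a definite share of the planned 0.5σ. The article does not support that, because neither the shift nor the SD of change in these marks is given.

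**What to change.** Define the academic outcome as the sum or mean of English, mathematics and home language. Report the life-skills mark separately, as a proximal measure that may not be comparable between arms. Keep the four-subject sum as a sensitivity analysis. State this before follow-up marks are examined by arm.

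Under the three-subject score, a shift in the life-skills mark contributes nothing directly to the outcome. Grades are obtained by subject, so no new data are needed, and no sample-size or power figure in the article changes. The cost is a slightly less reliable score from three subjects in place of four.

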#### KaziHealth Assessment Protocol

At baseline and follow-up testing, a comprehensive health risk assessment by health care personnel will be performed on the participating teachers via the *KaziChat*, a comprehensive health assessment tool, which will be used to capture and interpret all assessed health parameters. Internationally accepted cut-off and normative values will be used to rate each tested parameter based on a traffic light model. A personal health risk profile will be generated, with easy-to-understand explanations of the tested parameters as well as further referrals to a general practitioner, if needed.

### Anthropometry and Body Composition

Utilizing the same protocol as for *KaziKidz*, each participant’s body weight and height will be measured to calculate the BMI. Utilizing the same protocol as for *KaziKidz*, waist and hip circumferences will be measured to determine waist-to-hip ratio, a risk indicator for heart disease [39]. Bone mineral density and body fat percentage will be measured with the Discovery Hologic Dual-Energy X-ray Absorptiometry (DXA) QDR 4500A (APEX System Software Version 4.0.2) by a qualified radiographer. Pregnant individuals, individuals who underwent investigations using radioisotopes in the previous 10 days, and individuals with internal metal artifacts will be excluded from the DXA scan. Calibration will be conducted before testing, using the quality check test. Participant’s height, weight, gender, birth date, and ethnicity will be entered before the participant is instructed to lay supine on an open X-ray table within specified position boundaries. The participant will be instructed to lay still and breathe normally while the scan is being conducted, a process that takes approximately 7.5 min.

#### Clinical Measures

The clinical measures are as follows:

A detailed family and medical history will be taken from each participant by a health care professional. Current and previous signs or symptoms of cardiac disease (eg, myocardial infarction, palpitations, and arrhythmias), NCDs (eg, hypertension, dyslipidemia, and diabetes) and psychological conditions (eg, headaches, sleep disorders, and depression) will be recorded. The Physical Activity Readiness Questionnaire will be used to determine whether medical clearance from a general practitioner will be required before the physical fitness assessment [49].Each participant’s blood pressure will be measured 3 times after the participant has been seated for 5 min with a calibrated Omron digital blood pressure monitor (Omron M6 AC model; Hoofddorp, The Netherlands) for the detection of prehypertension and hypertension. A medium or large adult cuff size, 22 to 32 cm or 32 to 42 cm, respectively (Omron Medium and Large Cuff; Hoofddorp, The Netherlands) will be used depending on the participant’s arm circumference. The same protocol as indicated for *KaziKidz* will be followed to determine the final systolic and diastolic blood pressure values.Dyslipidemia and glycosylated hemoglobin will be tested with a POC instrument (Alere Afinion AS 100 Analyzer, Abbott Technologies; Abbott Park, United States of America) using a full lipid profile (TC, LDL-C, HDL-C, TG, non-HDL, and C-HDL ratio) and HbA1c test, respectively. The same protocol used for *KaziKidz* in this regard will also be applied for assessing these variables.For the detection of anemia, the hemoglobin concentration will be measured to the nearest 0.1 g/L, using a HemoCue Hb 301 system (HemoCue AB; Ängelholm, Sweden). The Eurotrol Hb 301 Control will be used to verify the precision and accuracy of the measuring device.

#### Physical Activity and Physical Fitness

Using the same protocol as for *KaziKidz*, physical activity behavior will be assessed with accelerometry. Cardiorespiratory fitness will be assessed through the Cooper 12-min run-walk test. The test is a simple, self-paced, maximal running test that is used to determine an individual’s maximal oxygen uptake (VO_2 _ max). The aim of the test is to run or walk as far as possible within 12 min. VO_2 _ max is then calculated with the following formula:

*VO*_2_ max (ml x kg^-1^ x min^-1^) = (*d*_12_ + 504.9)/44.73

where *d*_12_ refers to the total distance covered in 12 min in meters [50]. Before the test starts, blood pressure and heart rate are measured and a 10-min warm-up period is offered. All participants will receive the same instructions, and no verbal encouragement is allowed throughout the test. After the test is completed, a 5-min cool-down period will be given. Although all possible measures will be taken to reduce risk, all maximum exercise tests involve some risk. The test will be supervised by trained health care professionals with the necessary knowledge to deal with any medical emergency that may arise. Furthermore, an automated external defibrillator will be available on site.

Upper body strength will be determined with the handgrip resistance test utilizing the same procedure as described in the *KaziKidz* protocol.

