Our experiences with the DASH project also revealed that many South African teachers are at risk of cardiovascular diseases [29,30]. This insight was confirmed in a representative sample of South African educators (n=21,307) in public schools. Educators reported high stress levels, and there were significant associations between stress, lack of job satisfaction, and stress-related illnesses [31]. In South Africa, NCDs among adults have steadily increased. Indeed, although 42.90% (256,645/598,240) of deaths in 2005 were attributable to NCDs, the proportion rose to 57.40% (262,096/456,612) in 2016 [32]. Furthermore, in 2017, more than 1.8 million cases of diabetes were recorded in South Africa, representing 5.41% (1,826,100/33,762,000) of the adult population [33]. The project *Healthy Schools for Health Communities* presented here addresses this dual burden of disease, both in school children and teachers in South Africa (Figure 1).

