The primary objectives of the statistical analyses are (1) to assess the physical fitness of the participants and their associations with cognitive performance and psychosocial health at the beginning and over the course of the intervention, and (2) the effect of interventions on disease status and other health parameters. The secondary objective is to assess the feasibility and acceptability of the health interventions, as determined by FGDs.

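### The sign in the printed 12-minute-run formula appears to be wrong; if the constant should be subtracted, every teacher's absolute VO2max is 22.6 ml/kg/min too high

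*Protocol article*

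**What the plan says.** In the protocol article's section Physical Activity and Physical Fitness, teachers' cardiorespiratory fitness is measured by the Cooper 12-minute test. "The aim of the test is to run or walk as far as possible within 12 min", so walking distances are within the intended range. VO2max, in ml per kg per min, is then computed from the distance d12 in metres with the expression "d*_12_ + 504.9)/44.73", citing reference [50].

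The result is used in three ways:
- Assessment Methods lists "self-reported and objectively assessed physical activity and physical fitness" among the primary outcomes for the KaziHealth battery.
- KaziHealth Assessment Protocol states: "Internationally accepted cut-off and normative values will be used to rate each tested parameter based on a traffic light model". It adds that a personal risk profile is produced, with referral to a general practitioner where needed. Study Design says all teachers are told their profile after the baseline assessment.
- Data Collection and Statistical Analysis summarises fitness by mean and SD, or by median and interquartile range.

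The article prints no VO2max cut-off and no expected distance for teachers.

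**The concern.** The formula is a complete scoring rule that someone could apply as it stands, and its outputs look too high at realistic distances. A 12-minute walk at 5 to 6 km/h scores 34 to 38 ml/kg/min, and a 10 km/h run scores 56. The Background section says that "many South African teachers are at risk of cardiovascular diseases", so this is not a group in which such values would be expected as a matter of course. The pattern is what a reversed sign on the constant would produce.

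What is at stake is the absolute level: the fitness reported for the teachers, and the rating each teacher receives. An upward shift common to everyone moves ratings in the reassuring direction only.

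**Working it through.** **Inputs.** The constants 504.9 and 44.73, the plus sign and the unit (metres) come from Physical Activity and Physical Fitness. As a pace marker from within the article, the children's shuttle run is described as "Starting at a speed of 8.5 km/h" (Physical Fitness Tests); held for 12 minutes, that is 8500/5 = 1700 m. There is no VO2max figure in the article to reproduce.

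**Step 1: evaluate both signs.** Printed: (d12 + 504.9)/44.73. Reversed, by assumption: (d12 − 504.9)/44.73.

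| Distance (m) | Mean speed (km/h) | As printed | Sign reversed |
|---|---|---|---|
| 1000 | 5.0 | 33.6 | 11.1 |
| 1200 | 6.0 | 38.1 | 15.5 |
| 1500 | 7.5 | 44.8 | 22.2 |
| 1700 | 8.5 | 49.3 | 26.7 |
| 2000 | 10.0 | 56.0 | 33.4 |
| 2400 | 12.0 | 64.9 | 42.4 |

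**Step 2: size of the shift.** The two versions differ by 2 × 504.9/44.73 = 1009.8/44.73 = 22.6 ml/kg/min at every distance. At 1500 m the printed value is about double the reversed one.

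**Step 3: effect on a cut-off.** For a cut-off c, the distance needed is 44.73c − 504.9 as printed and 44.73c + 504.9 with the sign reversed, which is 1009.8 m more. The article gives no cut-off, so the values of c below are assumptions. The last two columns give the share of teachers above c, assuming normally distributed distances with mean 1100 to 1500 m and SD 200 or 300 m.

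| Assumed c | Distance needed, printed (m) | Distance needed, reversed (m) | Share above, printed | Share above, reversed |
|---|---|---|---|---|
| 25 | 613 | 1623 | 95–100% | 0–34% |
| 30 | 837 | 1847 | 81–100% | 0–12% |
| 35 | 1061 | 2070 | 55–99% | 0–3% |
| 40 | 1284 | 2294 | 18–86% | below 1% |
| 45 | 1508 | 2518 | 2–49% | about 0% |

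The direction is the same in every row. The number of teachers affected depends heavily on the assumptions.

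**Step 4: what cancels.** With either sign, follow-up minus baseline equals (d12 at follow-up − d12 at baseline)/44.73. The constant drops out of each teacher's change and so out of the between-arm difference. In a model with baseline as a covariate, the shift goes into the intercept and leaves the intervention coefficient alone. Linear slopes and correlations with continuous VO2max are likewise unchanged. Categories formed by a fixed cut-off are not protected in this way.

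**The case against.** **The evidence is indirect.** Reference [50] is not at hand, and the article offers no benchmark for what a teacher should score, so calling the values implausible is a judgement. The value at zero distance settles nothing: the printed form gives 11.3, but the reversed form is negative below 504.9 m, and both are odd outside the working range. This stands. It makes the point a strong reason to check rather than a proof, and the case rests on the values at ordinary walking and running distances.

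**It may be a misprint confined to the article.** Neither the KaziChat scoring nor the analysis code is shown, and either may hold the right formula. This also stands, so re-scoring and new feedback must depend on finding the error there. The printed formula would still need correcting. Fitness is also not the only route to referral, since blood pressure, lipids, HbA1c and medical history are assessed separately.

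**Two stronger readings are not supported.** A reader might infer that virtually every teacher would be rated fit. That needs cut-offs and distances the article does not give: it is roughly true at an assumed cut-off of 25, but at 45 only 2–49% would pass. A reader might also infer that the first primary objective, "to assess the physical fitness of the participants and their associations with cognitive performance and psychosocial health", is compromised. The associations are not, because a constant leaves them unchanged. The article lists cognitive measures only for children, whose VO2max comes from the shuttle run and a different formula. Only the description of teachers' absolute fitness is affected.

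**Conclusion.** The printed sign appears to be wrong. Assuming the constant should be subtracted, every teacher's absolute VO2max is 22.6 ml/kg/min too high: 44.8, 56.0 and 64.9 at 1500, 2000 and 2400 m, against 22.2, 33.4 and 42.4. If the printed rule is what is applied, reported fitness levels and traffic-light ratings would be systematically too favourable for the approximately 60 teachers, and some unfit teachers could be missed; their number cannot be derived from the article. The estimated intervention effect on continuous VO2max and all of the children's results are untouched. This should be corrected, but it does not threaten the trial comparison.

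**What to change.** 1. Check the sign against reference [50] before any further scoring.
2. If it is a minus, correct the formula in Physical Activity and Physical Fitness.
3. Check whether KaziChat and the analysis code use the printed sign. Only if they do, re-score the baseline values from the recorded distances and re-issue the affected fitness ratings. The Results section dates the baseline survey to January to March 2019, so ratings may already have gone out.
4. Report the 12-minute distance alongside VO2max, so that the result can be read without the conversion.

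The cost is one character in the text, a look at the scoring code and, if the error is there, an automatic re-score (provided the distances were kept) and corrected feedback to the teachers already tested. No new measurement is needed.
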